For individual missing responses on multiitem scales, we will compute scale scores by summing the available item scores as long as at least 80% of the item responses are available [67]. Missing data at the variable level will be handled through maximum likelihood imputation [67]. A concern with longitudinal research is that data are not missing randomly owing to systematic dropout. We will conduct attrition analyses to identify any factors systematically related to dropout and, if found, control for these effects in subsequent analyses. Any missing data that are random in nature, such as those that occur owing to random mistakes in data collection or entry and are not related to research staff or patient noncompliance, will be submitted to maximum likelihood estimation procedures to estimate those missing values. Maximum likelihood estimation for random missing data is a common and accepted procedure for missing data estimation [68,69]. If specific patterns of missing data are identified, we will further address missing values with multiple imputation. Multiple imputation will maximize accurate statistical inferences and allow for valid statistical inferences by appropriately accounting for the uncertainty caused by missing data [68,69].

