## Results

The study was funded in January 2021. Data collection started in May 2021 and ended in mid-2022. In total, 103 dyads were matched at the beginning of the intervention. Of the 103 dyads, 90 (87.4%) dyads completed the midtest survey and 64 (62.1%) dyads completed the posttest survey. Although a total of 92 dyads were planned to test the effectiveness of the intervention in this proposed study, the post hoc power analyses performed using G*Power 3.1.9 indicated that 64 dyads will yield sufficient power to test the interaction between groups over time (power=0.95), the changes over time (power=0.95), and the differences between the groups (power=0.71). These parameters are based on a small anticipated effect size (*f*=0.22), α=0.05, two-tailed, with measures correlated at r=0.30.

We also collected qualitative interview data for this study with selected dyads in the intervention group (8/27, 30%). Weekly reflection page from UTA student participants, weekly fidelity check forms, final digital story books, and final scrapbooks were also saved for future data analyses. We are currently engaged in data cleaning and analysis for both quantitative and qualitative data. One manuscript has already been published [73], and we anticipate publishing several more manuscripts reporting the results within the next 1-2 years.

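### The missing-data text prescribes maximum likelihood imputation of missing scores; taken literally this understates standard errors, and the remedies for systematic dropout cover only dropout explained by observed data

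*Protocol article*

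**What the plan says.** All the relevant rules are in the Data Collection Plan of the protocol article.

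- General rule for missing variables: "Missing data at the variable level will be handled through maximum likelihood imputation". The sentence is not limited to any type of missingness.
- Gaps regarded as random, "such as those that occur owing to random mistakes in data collection or entry and are not related to research staff or patient noncompliance": these "will be submitted to maximum likelihood estimation procedures to estimate those missing values".
- Dropout: "A concern with longitudinal research is that data are not missing randomly owing to systematic dropout". The response is "We will conduct attrition analyses to identify any factors systematically related to dropout and, if found, control for these effects in subsequent analyses".
- Conditional step: "If specific patterns of missing data are identified, we will further address missing values with multiple imputation". Only here does the text claim that uncertainty from missing data is carried into the inference.

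The Statistical Analysis section then compares the arms with covariate-adjusted linear mixed models for repeated measures. The Results section reports 103 matched dyads, 90 at midtest, and that "64 (62.1%) dyads completed the posttest survey". The sample size allowed for 5% attrition.

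**The concern.** Two things are wrong with the text as written.

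First, imputing by maximum likelihood and estimating the missing values describes filling in scores, not estimating model parameters from incomplete records. If one value is put in each gap and the mixed model treats it as data, the sample looks larger and less variable than it is. Standard errors are then too small and confidence intervals too narrow. The step is also unnecessary, because a likelihood-based mixed model uses incomplete records as they stand.

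Second, the section names data that are not missing randomly and answers with two tools that both assume missing at random. A reader could believe that the case is dealt with when only part of it is.

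Both points matter much more at 37.9% posttest loss than at the 5% attrition planned for.

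**Working it through.** **The article's own figures.** 90/103 = 87.4% at midtest (12.6% lost) and 64/103 = 62.1% at posttest (37.9% lost). Both match the Results section. These count dyads, so loss among individuals may be lower.

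**Rough calculation for a single fill-in.** Let p be the share of scores observed. The true variance of a group difference is proportional to σ²/(np). Filled-in values lie on the fitted regression and add no residual scatter, so the reported variance is roughly proportional to pσ²/n. The ratio of reported to true standard error is therefore about √(p × p) = p, and the type I error is about 2[1 − Φ(1.96p)].

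- Posttest, p = 0.621: 1.96 × 0.621 = 1.22, giving about 22%.
- Midtest, p = 0.874: 1.96 × 0.874 = 1.71, giving about 8.7%.
- 5% missing, p = 0.95: 1.96 × 0.95 = 1.86, giving about 6.3%.

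**Simulation.**
- From the article: 103 pairs, two-sided α = 0.05, r = 0.30 between waves.
- Assumed: a 52/51 split, three waves with SD 1 and equal correlations, r = 0.60 as an upper value, and the dropout mechanisms.
- Analysis: posttest compared between arms, adjusted for baseline, with no true effect.
- Runs: 1,000 per setting for single fill-in and multiple imputation (20 imputations, Rubin's rules), 4,000 per setting for fill-in at varying shares missing, and 300 for the mixed model.

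| Method | Missing at posttest | SE ratio | Type I error |
|---|---|---|---|
| Single ML fill-in | about 38%, completely at random or dependent on baseline | 0.61–0.67 | 18–23% |
| Single ML fill-in | 12.6% | 0.88 | 8–9% |
| Single ML fill-in | 2–5% | 0.94–0.98 | 5–7% |
| Mixed model, observed scores only (r = 0.30) | dependent on baseline | 1.01 | 6.7% |
| Standard multiple imputation | about 38%, completely at random or dependent on baseline | 0.98–1.02 | 4.6–5.8% |
| Standard multiple imputation | dependent on the unseen posttest score in one arm | 0.98–1.04 | 15–22% |

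For example, at r = 0.30 with loss completely at random, single fill-in reports a mean SE of 0.149 where the estimate's actual SD is 0.238. The 6.7% for the mixed model has a simulation error of √(0.05 × 0.95/300) = 1.3 percentage points, so it is compatible with 5%. In the last row the excess comes from bias of 0.19 to 0.28 SD, not from a wrong standard error.

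**The case against.** The strongest reply is that the text is loose rather than wrong. It uses maximum likelihood imputation and maximum likelihood estimation almost interchangeably and never says single imputation. The planned mixed model is itself likelihood-based. If that is what was meant, standard errors are correct. This stands: the defect depends on the literal reading. But the words do say that values are imputed and estimated, and an analyst following them would fill in scores.

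The sentence about estimating missing values is confined to random collection or entry errors. At a few percent missing the harm is small. This also stands. The link to dropout rests on the unrestricted sentence about variable-level missing data.

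The plan does respond to systematic dropout. Attrition covariates and multiple imputation handle dropout explained by observed factors, so it would be wrong to say that the plan ignores the problem. If multiple imputation is triggered and replaces the filled-in values, its standard errors are valid under missing at random. A tipping-point analysis may sit in the SAP, which is not shown, so its absence is not counted here.

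Three stronger readings are tempting and not supported.

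- **Unequal loss by arm.** A reader might take the denominator in "selected dyads in the intervention group (8/27, 30" as the intervention completers at posttest, leaving 64 − 27 = 37 controls. The article does not say that 27 is that count and gives no split of the 103. Fisher's test on those numbers gives p = 1.0 at 44/59, 0.31 at 48/55, 0.07 at 51/52 and 0.009 at 54/49, so nothing follows.
- **Every outcome has anti-conservative inference.** This holds only under the fill-in reading.
- **The preliminary results rest on completers alone.** The article does not say how they were obtained.

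**Conclusion.** The point holds, conditionally on its first part. As written, the general rule is imputation by maximum likelihood with no allowance for imputation uncertainty unless a later, conditional step is reached. At the reported posttest loss that means standard errors about 33 to 39% too small and a type I error of 18 to 23%, in a baseline-adjusted comparison with the assumed split, correlations and dropout mechanisms above. Under direct likelihood there is no numerical error and the wording alone needs correcting.

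The second part does not depend on that reading. Covariate control and standard multiple imputation leave dropout that depends on unseen outcomes uncovered, although the section raises data not missing randomly. The bias of 0.19 to 0.28 SD illustrates one such mechanism. It is not an estimate for this trial.

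**What to change.** Replace the imputation sentences with a statement that the mixed model is fitted by REML to all observed scores of all randomised participants with a baseline, with no filled-in values. This keeps the midtest scores of at least 90 − 64 = 26 dyads that have no posttest.

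Limit covariates taken from the attrition analyses to baseline variables. The present wording does not propose post-baseline factors, but it does not exclude them, and adjusting for factors that treatment can affect may bias the comparison.

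State that multiple imputation is valid under missing at random. Use it for sensitivity analysis, with delta-adjusted departures varied separately by arm, if the SAP does not already provide this.

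The cost is a few sentences and a few extra model runs. The article says analysis was still under way, so the change could be made in time. Confidence intervals would be wider than a fill-in would report, by a factor of about 1/0.67 = 1.5 to 1/0.61 = 1.6 at posttest. If direct likelihood was always intended, the intervals do not change.

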### Statistical Analysis

After data are collected and entered into the statistical software, data quality will be carefully reviewed and then checked both automatically and manually. The review processes involved in data management encompass several steps. These include cross-checking the coding of observations or responses and identifying out-of-range values; ensuring data completeness; adding variable and value labels as needed; verifying random samples of digital data against the original data; implementing double entry of data; conducting statistical analyses such as determining the frequencies, means, and ranges to identify errors and unusual values; and rectifying any errors made during transcription. In addition, data will be thoroughly reviewed to address concerns related to the protection of human participants and confidentiality. This includes assessing the risk of potential disclosure of research participants’ identities, safeguarding sensitive information, and preserving the privacy of the collected data. As all the key concepts in the proposed study are measured using standard scales, reliability tests for each scale and test-retest reliability across the 4 surveys will be conducted.

For quantitative data analyses, descriptive analyses will first be conducted to provide the overall means and frequencies of key outcome variables for both older and young participants in the intervention and control groups. Fisher exact tests, Pearson chi-square tests, and independent samples *t* tests (2-tailed) will be computed to test for group differences that may be attributable to participants, such as age, sex, education level, income, and health conditions. If the groups significantly differ on any of these variables, the variable will be incorporated into the following analyses as a covariate, thereby controlling for potential influences that the covariate may have on the dependent variables. Moreover, in the event that at the culmination of this study, our sample sizes are unequal in the treatment groups or our outcome data are nonnormal, we will follow through with appropriate statistical corrections where necessary. Covariate-adjusted linear mixed models for repeated measures will be performed to compare the intervention and control groups over time for the major outcomes of older adults and young adult volunteers. The covariate will be any significant variable yielded from the univariate analyses, and the dependent variable will be the scores before the intervention, in the middle of the intervention, at the end of the intervention, and at 3-month follow-up. In this study, 95% CIs will be computed for each adjusted mean difference. The study α will be set to .05, with no adjustments for multiple comparisons owing to the preliminary nature of this study and the increased risk of type-2 error as a result of α adjustment [70].

Several different combinations of statistical results are possible. The results may indicate that the intervention and control groups significantly differ in outcomes among the older participants and the young adult volunteers. Another possibility is that differences may be discovered for one age group but not the others. Outcome measures may significantly change over time for none of the groups, some groups, or all groups. Another possibility is that the pattern of change over time for one group may not replicate in another group. This possibility, which would be identified via a significant interaction in linear mixed models, would require post hoc testing to investigate the nature of changes over time. In this case, groups will be isolated, and patterns of change will be identified via linear mixed models for repeated measures (with no between-participants factors). *For the qualitative data analysis*, the process will involve digitally recording and transcribing the qualitative interviews, followed by using conventional content analysis, as outlined by Hsieh and Shannon [71]. The research team, including LX and [name], along with the research assistants, will independently code the data, forming the foundation for an initial coding framework. Subsequently, the researchers will convene to compare and establish consensus on the coding outcomes. Pertinent excerpts from the transcripts will be extracted and reorganized based on thematic relevance. The constant comparison process, as described by Glaser and Strauss [72], will be used to explore similarities and differences among participants who did and those who did not benefit from the intervention, generating subthemes within the broad topics. This comparative approach will enhance consistency and broaden the dimensions and comprehensiveness of each code. Eventually, the codes will be synthesized or combined into overarching recurrent themes. During the analysis stage, themes, research notes, and field notes will be reviewed using thematic charts. Multiple strategies, including peer debriefing, will be implemented to address potential investigator bias and enhance the study’s credibility. Maintaining comprehensive documentation will also ensure that an audit trail is available for future reference.

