## Methods

### Study Design

The proposed project will conduct a randomized controlled trial to assess the effects of the intergenerational reminiscence approach with DST on the social and emotional well-being of older adults with ADRD. An explanatory sequential mixed methods design [39] will be used, which first involves collecting quantitative data and analyzing the data to identify subsamples of participants who report the greatest and least changes and then conducting qualitative interview with these subsamples. Half (46/92, 50%) of the dyad sample will receive the reminiscence DST intervention, and the other half (46/92, 50%) of the sample will receive a regular social visit from young adult volunteers without the intervention. Dyads will be randomly assigned to either the intervention or control group after baseline screening of all participants and, subsequently, randomly matched within each group. To further prevent selection bias, statistical techniques such as covariate-adjusted linear mixed models will be used to adjust for covariate imbalance during data analysis.

A total of 92 dyads are required to test the effectiveness of the intervention in this proposed study (refer to power analysis in the *Sample and Recruitment Plan* section). We will recruit participants on a rolling basis until we recruit 92 dyads. At least one-fourth (23/92, 25%) of the total sample of older adults and young adult volunteers will be recruited before they are randomly matched. Upon signing the consent form, participants will be given the chance to engage in the study. They will be provided with guidance throughout the informed consent process and will subsequently undergo a baseline survey in which all measures will be collected blind to group conditions.

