### Data Management and Participants’ Safety

The research team will be the sole individuals with knowledge about and access to the names of both the older and young participants. Although certain demographic information, such as age, sex, and racial and ethnic background, may be recorded, the questionnaires will not contain any participant identifiers such as date of birth or address. The preintervention and postintervention questionnaires will also be devoid of participant identifiers. To ensure confidentiality, participant names will be deidentified, with each individual assigned a unique study identifier or number. All data files will be securely stored in encrypted, password-protected folders on laptops provided by UTA. These laptops will also have encryption in accordance with the guidelines set by the UTA Office of Information Technology. Participant privacy will be diligently safeguarded, and records containing names and other identifiable information will be stored separately from the interviews, using password-protected, encrypted files on UTA-issued laptops. The PI (LX) and the UTA institutional review board (IRB) will bear the responsibility of ensuring participant safety and the attainment of the study’s scientific objectives. The research team possesses previous experience in organizing and managing clinical trials, including implementing data safety monitoring measures for interventions.

All the older adults and young adult volunteers will provide informed consent before participating in the study. Potential participants will be informed that refusal to consent to the study or withdrawing from the study will have no effect on the services that they currently receive or might receive through UTA (ie, young adult volunteers) or through MOW or the Area Agency on Aging (ie, older adults). Participants who provide informed consent will be contacted for baseline measurement and then randomized to 1 of the 2 treatment groups. The protocol and consent forms will be approved by the UTA IRB before conducting any study procedures. Student members of the research team will receive training regarding procedures required to obtain informed consent.

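### Covariates are chosen by significance tests of baseline differences between randomised arms, so the adjustment performs like none and forgoes precision; type I error is not inflated

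*Protocol article*

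**What the plan says.** The rule stands twice in the Statistical Analysis section. Baseline comparisons come first: "Fisher exact tests, Pearson chi-square tests, and independent samples *t* tests (2-tailed) will be computed to test for group differences", on characteristics "such as age, sex, education level, income, and health conditions". Then: "If the groups significantly differ on any of these variables, the variable will be incorporated into the following analyses as a covariate". The description of the mixed model repeats it: "The covariate will be any significant variable yielded from the univariate analyses". The same section sets the significance level: "The study α will be set to .05, with no adjustments for multiple comparisons".

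The Study Design section gives the purpose: "To further prevent selection bias, statistical techniques such as covariate-adjusted linear mixed models will be used to adjust for covariate imbalance during data analysis". The order of events is in Data Management and Participants' Safety: "Participants who provide informed consent will be contacted for baseline measurement and then randomized to 1 of the 2 treatment groups".

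The article names no covariate to be included on prognostic grounds. Two other routes into the model, factors found to relate to dropout (Data Collection Plan) and documented contamination (Procedure), also depend on the data. The baseline score of each outcome is one of the repeated scores making up the dependent variable, so it does not depend on the rule.

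**The concern.** In a randomised trial the value of a covariate lies in its relation to the outcome. A test comparing the arms at baseline carries no information on that. The rule leaves out a strongly prognostic variable with p = 0.06 and takes in an irrelevant one with p = 0.04. Randomisation already protects against selection bias at allocation; what adjustment chiefly adds is precision, and a rule that nearly always omits the useful variables gives that up.

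The plan also pulls in two directions. It waives multiplicity adjustment because it fears type II error, yet it selects covariates in a way that forgoes power the collected data could supply. And the form of the final model is settled by which baseline tests happen to reach 0.05.

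**Working it through.** **Inputs from the article.** Randomisation after baseline; five named variables in an open-ended list; α = 0.05; 46 dyads per arm planned, 64 dyads with a posttest survey (taken as 32 per arm); f = 0.22; r = 0.30; four measurements. Covariate-outcome correlations are not given. They are assumptions and are shown over a range.

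**1. The plan's own figure.** For the between-group test, λ = f²·N·m / (1 + (m − 1)r) = 0.0484 × 64 × 4 / 1.9 = 6.52, with 1 and 62 degrees of freedom. Power is 0.710, which matches the 0.71 in the Results section.

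**2. How often a variable enters.** Under randomisation the t test flags a variable with probability 0.05 (simulated 0.049 to 0.052), whatever its prognostic strength. With Fisher's exact test the probability is about 0.03. For a continuous variable the observed imbalance must exceed about 0.41 SD at 46 per arm, or 0.50 SD at 32 per arm. Taking the variables as independent:
- five variables: none enters with probability 0.95^5 = 0.774, at least one with 0.226;
- five in each age group: 1 − 0.95^10 = 0.401 that at least one enters somewhere.

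**3. Effect of the rule.** Simulation of one post-treatment score and one covariate at 46 per arm, 40,000 runs per cell, effect set for about 80% unadjusted power:

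| Assumed correlation | Unadjusted power | Stated rule | Fixed in advance | Type I error, stated rule |
|---|---|---|---|---|
| 0.3 | 0.79 | 0.79 | 0.82 | 0.048 |
| 0.5 | 0.79 | 0.80 | 0.89 | 0.045 |
| 0.7 | 0.79 | 0.81 | 0.97 | 0.035 |

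The rule tracks the unadjusted analysis throughout, and results at 32 per arm are nearly the same. The last row is not compatible with this trial's assumptions: a covariate correlated ρ with every score implies a correlation between scores of at least ρ², and 0.7² = 0.49 exceeds r = 0.30.

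**4. Size within r = 0.30, for the comparison of level.** The variance of a person's mean of four scores is (1 + 3 × 0.30)/4 = 0.475. Covariates with squared correlations summing to R² reduce it to 0.475 − R². Fitting five covariates in 64 people raises the variance of the group contrast by roughly 61/56 = 1.09. So λ ≈ 0.0484 × 64 / (0.475 − R²) / 1.09, with 57 residual degrees of freedom:
- correlations 0.2 and 0.1, three irrelevant: R² = 0.05, λ = 6.69, power about 0.72;
- correlations 0.3 and 0.2, three irrelevant: R² = 0.13, λ = 8.24, power about 0.81;
- all five irrelevant: λ = 5.99, power about 0.67.

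Simulation gave about 0.71 and 0.81 for the first two cases, against about 0.69 unadjusted.

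**5. Group-by-time test.** With complete data a time-constant main effect cancels from within-person contrasts. In a random-intercept model fitted to one simulated data set (64 people, four visits), the interaction estimates were identical with and without the covariates, and the SE was 0.257 both ways. Adding five covariates to a change-score comparison moved power from about 0.52 to 0.48.

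**6. Use of the baseline score.** At r = 0.30 the variance of change from baseline is 2(1 − 0.30) = 1.40, and that of the posttest score adjusted for baseline is 1 − 0.30² = 0.91. In simulation, adjusting the posttest score for baseline gave power of about 0.68 against 0.52 for change from baseline.

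**The case against.** The strongest reply is that the rule does little harm. It is stated in advance, it selects on participant characteristics and not on outcomes, and it does not inflate type I error. The baseline score, probably the strongest predictor, is already in the response vector. All of this stands, and it limits the point to precision and to a model not fixed in advance.

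A second reply is that differences among completers may reflect dropout and not chance alone. That is possible if the tests are run on the 64 of 103 dyads with a posttest survey. But a p value is then no better a guide to which variables predict the outcome, and the Data Collection Plan handles dropout factors separately.

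A reader might infer four stronger things, which the article does not support:
- **False positives.** The simulated type I error under the rule is at or below 0.05.
- **A large power gain.** A simulation of a single visit with covariates correlated 0.5 and 0.3 with the outcome moves power from 0.51 to 0.67. But those values imply a correlation over time of at least 0.25 + 0.09 = 0.34, above the plan's 0.30.
- **A gain on the group-by-time test.** Main-effect covariates leave it unchanged.
- **Dropout makes the rule worse.** The loss of 38% of dyads (39 of 103) does not change how the rule works.

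Nor is it a fault in itself that the two age groups could have different covariates: they are different populations with partly different outcomes.

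**Conclusion.** The point holds as one of precision and prespecification. In the randomised set the rule admits each variable about 5% of the time, regardless of prognostic value, and performs like no adjustment. Under the plan's f = 0.22 and r = 0.30 at 64 dyads, what is forgone on between-group comparisons of level runs from almost nothing (about 0.70 to 0.71) to a useful amount (about 0.81), depending on assumed correlations that the article does not give. Nothing is forgone on the group-by-time test, and the validity of the tests is not threatened. The change is worth making because it is cheap and uses variables already collected, and because the between-group comparison is the weakest of the three in the article's own post hoc calculation (0.71, against 0.95 and 0.95).

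**What to change.** - Delete both statements of the significance-test rule. Report baseline characteristics by arm descriptively, without tests.
- For each age group, name a short prognostic covariate set and include it whatever the baseline p values: for example age, sex, education and self-reported health, plus the AD8 score for older adults. The first four are in the pretest survey, and the AD8 is used for eligibility.
- Use the baseline outcome score once. Either enter it as a covariate with only the later scores as the response, or keep it in the response vector with baseline means constrained equal between arms. It should not stand on both sides of the model.
- The Results section says that analysis is under way and one manuscript is published. State the date of the change, and report the analysis under the stated rule as a sensitivity analysis.

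**Cost.** No new data. A few degrees of freedom are spent, with a small power loss if the covariates prove unrelated to the outcome (about 0.71 to 0.67 with five useless ones at 64 dyads), which is a reason to keep the list short. The handling of the baseline score is a change to the model and not only to its wording.
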